The initial analysis will evaluate the mean percent change between EBV and control in FEV_1 _and 6 MWT using an unpaired t-test if data are normally distributed or Mann-Whitney-Wilcoxon test if data require non-parametric testing. To determine if covariates impact the primary outcome variables, and to adjust for potential imbalances in randomization, both primary endpoints will be further tested via a multivariate model (SAS PROC MIXED). In order to reduce the possibility of over-specification of the model, the potential covariates listed in Tables 6, 7, 8, 9 will be subjected to a univariate screening procedure similar to that described by Hosmer and Lemeshow[20]. Derivations for these variables are provided in Table 10. Main effects and interactions with a p-value of 0.15 or less are allowed to enter a multivariate analysis using a mixed linear model (SAS PROC MIXED). The treatment effect must remain in the model in order to substantiate the one-tailed test of superiority. Those variables found to have statistically significant interactions with the treatment arm via the mixed model analysis will be further analyzed in follow-on sub-group analyses. In order to limit the impact of multiple hypothesis testing, univariate sub-set analysis will be performed using only those independent variables that remain in the mixed model as interactions with the treatment arm. For those analyses performed on the remaining independent variables, appropriate adjustments will be made to account for impact on Type I error[11]. Secondary endpoint analyses will follow the same methodology as described above.

**Table 6 T6:** Plethysmography, spirometry and HRCT derived baseline potential covariates*

Variable	Plethysmography/Spirometry	HRCT at TLC	HRCT at RV	TLC and RV HRCT ^†^
RV	X			
RV % Predicted	X			
TLC	X			
TLC % Predicted	X			
RV/TLC	X			
VC	X			
FVC	X			
FVC % Predicted	X			
FEV_1_	X			
FEV_1 _% Predicted	X			
FEV_1_/FVC	X			
Destruction Score of Target Lobe		X	X	
Ipsilateral Heterogeneity^††^		X	X	
Whole Lung Heterogeneity^††^		X	X	
For RUL Treatment Subset only: RUL-RML Heterogeneity^††^		X	X	
Target Lobe Volume % of TLC		X		
Target Lobe Volume % of RV			X	
Max Destruction Score other than target		X	X	
Min Destruction Score other than target		X	X	
Target Lobe Destruction Score % TLC-RV Delta				X
Target Lobe Volume % TLC-RV Delta				X
Fissure Score^†††^		X		

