*Variables marked in multiple columns will be calculated twice, once using the expiratory (RV) CT and once using the inspiratory (TLC) CT. All tests are at Baseline.

^†^Some variables require information from both the TLC and RV CT

^†† ^Heterogeneity scores are derived by subtracting the minimum destruction score from the maximum destruction score.

^††† ^Fissure Score is an integer scale from one to three base on visual scoring by core center radiologists (1 = Fissure Absent, 2 = Incomplete Fissure, 3 = Complete Fissure).

**Table 7 T7:** Other baseline and procedure potential covariates

	Baseline	Procedure
Gender	X	
Age	X	
Site	X	
6 MWT	X	
Cycle Ergometry	X	
BMI	X	
DLCO % Predicted	X	
PaO_2_	X	
PaCO_2_		
Target Lobe		X
RUL Treatment		X
Upper vs. Lower		X
Right vs. Left		X
Valve Version*		X
Large Valve*		X
Small Valve*		X
Valve Combos*		X
Valve Expectorated*		X

*These potential covariates apply only to the treatment arm and do not have a control arm subset.

**Table 8 T8:** Composite or other potential covariate interactions

Composite or Interactions	Definition
Baseline BODE	BMI, FEV_1_% predicted, MMRC, 6 MWT Composite Score
NETT Strata	Randomization Stratification by Baseline Cycle Ergometry and HRCT at TLC
NETT Strata by Right vs. Left	Randomization Stratification by Baseline Cycle Ergometry and HRCT at TLC, by Right or Left Lung
Lobar Exclusion by Fissure Interaction*	Fissure Score = 3 AND Lobar Exclusion = Yes vs. all others
Lobar Exclusion, Fissure, and RV % Predicted*	Lobar Exclusion = Yes AND Fissure Score = 3 AND RV % Predicted ≥ 200% vs. all others
Lobar Exclusion, Fissure, and RV % Predicted*	Lobar Exclusion = Yes AND Fissure Score = 3 AND RV % Predicted ≥ 200% vs. all others
Large Valve by Right vs. Left*	Right vs. Left Lung AND Large Only vs. Others
Small Valve by Right vs. Left*	Right vs. Left Lung AND Small Only vs. Others
Expectorated Valve Replaced*	Valve(s) Expectorated AND Lobar Exclusion = Yes vs. all others
Expectorated Valve Not Replaced*	Valve(s) Expectorated AND Lobar Exclusion = No vs. all others
Lobar Exclusion by Site*	Technical Success by Site
First Case by Site*	First Treatment Case by Site vs. All Others
Learning Curve by Site*	Experience Level: Case 1, vs. 2 & 3, vs. 4–6, vs. 7–9, vs. ≥10 by site.

*These potential covariates apply only to the treatment arm and do not have a control arm subset.

**Table 9 T9:** 180 day follow-up CT potential covariate*

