Variable	180 Day HRCT at TLC	Baseline and 180 Day HRCT at TLC	Baseline and 180 Day HRCT at RV
Target Lobe Atelectasis Score^†^		X	X
Lobar Exclusion^†† ^(yes/no)	X		

*These potential covariates apply only to the treatment arm and do not have a control arm subset.

^†^Atelectasis Score is a continuous variable from 0 to 100% and is defined as the % volume change in the target lobe from baseline to 180 day follow-up.

^††^Lobar Exclusion will be determined by the core lab radiologists and is defined as all airways into the target lobe are occluded by valves at day 180.

**Table 10 T10:** Covariate variable derivations

**Variable**	**Definition**
RV	Residual Volume by Spirometry and Plethysmography (TLC - Max (FVC or VC))
TLC	Total Lung Capacity by Plethysmography
VC	Vital Capacity by Plethysmography
FVC	Forced Vital Capacity by Spirometry
FEV_1_	Forced Expiratory Volume in the First Second by Spirometry
Target Lobe	RUL, RLL, LUL, or LLL
RUL	RUL Target vs. Others
Density Score	Density Score by Lobe
Total Density Score	Sum of all Lobar Density Scores (including RML)
Ipsilateral DS Heterogeneity	Target - Max DS of Non-treated Lobes within Treated Lung [e.g.: RUL - Max(RML, RLL)]
Thorax DS Heterogeneity	Target DS - Max DS of All Non-treated Lobes [e.g.: RUL - MAX (RML, RLL, LUL, LLL)]
Target Lobe DS % Delta	(TLC HRCT - RV HRCT)/TLC HRCT Density Score of Target Lobe
Target Lobe Volume % Delta	(TLC HRCT Volume - RV HRCT)/TLC HRCT Volume of Target Lobe
Fissure Score	Categorical Fissure Assessment Surrounding Target Lobe
	1 = Absent
	2 = Incomplete
	3 = Complete
NETT Strata	1 = Upper-Lobe Predominance, Low Baseline Exercise Capacity*
	2 = Upper-Lobe Predominance, High Baseline Exercise Capacity
	3 = Non-Upper-Lobe Predominance, Low Baseline Exercise Capacity
	4 = Non-Upper-Lobe Predominance, High Baseline Exercise Capacity
Target Lobe Atelectasis Scores	% change in Target Lobe Volume at TLC and at RV between Baseline and 180-day HRCT
Lobar Exclusion	Yes, If all bronchial pathways to target lobe are sealed by valve(s) – adjudicated by HRCT Core Lab
Valve Combinations	1. Small ONLY
	2. Small AND Large
	3. Large Only
Large Valve	Any procedure with Only Large Valves vs. all others
Small Valve	Any procedure with Only Small Valves vs. all others

*Low Exercise Capacity by Cycle Ergometry ≤ 25 W for Women, ≤ 40 W for Men

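### The adjusted model meant to substantiate superiority can admit valve-arm-only and day-180 covariates, after which its treatment term no longer estimates the randomised effect

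*Protocol article*

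**What the plan says.** The Analysis section sets out two steps for the co-primary endpoints (percent change in FEV1 and in six-minute walk distance at 180 days). The first is a covariate-free comparison of the arms by t-test or Mann-Whitney-Wilcoxon test. The second is a SAS PROC MIXED model, intended both to see whether covariates affect the outcomes and to correct for chance imbalance between the arms.

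For the second step, "the potential covariates listed in Tables 6, 7, 8, 9 will be subjected to a univariate screening procedure". The entry rule is: "Main effects and interactions with a p-value of 0.15 or less are allowed to enter a multivariate analysis using a mixed linear model". The model is tied to the main claim: "The treatment effect must remain in the model in order to substantiate the one-tailed test of superiority".

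A footnote to the starred rows of Tables 7 and 8, and to the whole of Table 9, reads: "These potential covariates apply only to the treatment arm and do not have a control arm subset". Lobar exclusion, in Table 9, "is defined as all airways into the target lobe are occluded by valves at day 180". The atelectasis score is the change in target-lobe volume from baseline to day 180. The primary outcomes come from the 180 ± 14 day visit (Treatment group section), and the primary cohort is declared intent to treat.

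**The concern.** A model that adjusts a randomised comparison for imbalance should contain only what was fixed before randomisation. Here the candidate list mixes baseline variables with variables that exist only because a patient was assigned to and received valves, and no rule keeps the two apart. Lobar exclusion is a likely entrant: the Treatment group section itself says that one unoccluded segmental airway may reduce the benefit.

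Once such a variable is in the model, its treatment term answers a question that randomisation does not protect. Because the article asks this model to substantiate superiority, a sound unadjusted result could appear to be contradicted, or an unsound one could appear to be supported.

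**Working it through.** **Candidates.** Counting inspiratory and expiratory CT versions separately, and the Table 8 row that is printed twice once:
- Table 6: 28, all baseline.
- Table 7: 13 available in both arms and 5 starred.
- Table 8: 3 available in both arms and 9 distinct starred.
- Table 9: 3, all valve-arm only.

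Total: 28 + 18 + 12 + 3 = 61, of which 28 + 13 + 3 = 44 are available in both arms and 5 + 9 + 3 = 17 in the valve arm only. Target lobe, side and upper/lower are listed under Procedure, but they follow from the baseline CT in both arms and are not part of the problem.

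**What the treatment coefficient becomes.** Let T be the arm (1 = valve) and E lobar exclusion. The article does not say how E is set in controls, so take both possibilities.

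1. *Controls coded 0.* The model y = b0 + bT·T + bE·E has three cells: controls b0, valve patients without lobar exclusion b0 + bT, and valve patients with it b0 + bT + bE. Hence bT = mean(valve, E = 0) − mean(all controls). The product T·E equals E, so no separate interaction exists. With p the proportion achieving lobar exclusion, the randomised effect is bT + p·bE, so bT = randomised effect − p·bE.
2. *Controls missing.* Complete-case fitting drops the whole control arm, and bT cannot be estimated.

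**Size: inputs.** The plan states no figure for this model, so there is none to reproduce. From the Analysis section: FEV1 SD 33.7, target effect 15%, at least 270 subjects at 2:1 (180 and 90), one-sided 0.025. Assumed, because the document does not give them: p = 0.3, 0.5 or 0.7, and the size of the difference between patients with and without lobar exclusion.

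**Unadjusted reference.** SE = 33.7 × √(1/180 + 1/90) = 4.35. 15/4.35 = 3.45. Power = Φ(3.45 − 1.96) ≈ 0.93.

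**Scenario A: true effect 15%, 10 points larger with lobar exclusion.** bT = 15 − 10p, and SE = 33.7 × √(1/[180(1 − p)] + 1/90).

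| p | bT | SE | Power for treatment term |
|---|---|---|---|
| 0.3 | 12 | 4.65 | 0.73 |
| 0.5 | 10 | 5.02 | 0.51 |
| 0.7 | 8 | 5.80 | 0.28 |

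A simulation (4,000 trials per row) that applied the p ≤ 0.15 entry rule to lobar exclusion gave the same powers. The variable entered in 92% to 99% of trials.

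**Scenario B: no treatment effect, but a prognosis 15 points better without lobar exclusion.** Here bE = −15, so bT = 15p = 4.5, 7.5 and 10.5 if E always enters. With the entry rule applied, the simulated mean of the treatment term was 4.2, 7.1 and 8.6, and one-sided type I error was 0.14, 0.29 and 0.34. The unadjusted test stayed at 0.024 to 0.028. With the prognostic gap reversed, the means were −4.3, −6.9 and −8.4, and rejection was close to 0.

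**Scenario C: no effect and no gap.** The treatment term was unbiased.

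**The case against.** - *The randomised comparison comes first and contains no covariates.* This stands. The success rule (both endpoints, one-sided p < 0.025) can be met and read from that comparison alone. A reader might infer that the primary analysis as a whole is invalid; the document does not support that.
- *The sentence on keeping the treatment effect may only mean that the arm term is never screened out.* It can be read so. A reader might instead infer a significance gate that a real benefit could fail, and the stated purpose of substantiating the superiority test lends that some support, but the wording does not settle it. Forced retention would not repair the coefficient once a valve-only variable is present.
- *The footnotes disclose that the starred variables have no control-arm counterpart, which hints at within-arm use.* This mitigates only in part, because the screening sentence sends all four tables into the same model.
- *Not every starred variable is a consequence of treatment.* Agreed. Valve version, first case and learning curve describe the device or the operator. Expectoration, lobar exclusion and atelectasis are the clear post-treatment variables. All are unfit for this model, because none is defined in controls.
- *The statistical analysis plan may settle the matter.* The point does not rest on an omission: the article names the variables, the entry rule and the role of the model.

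Two further inferences are tempting and should not be drawn. The article does not say that covariates in interactions are left uncentred. Nor does it say that the promised type I error adjustment for subsets counts only the variables that survive screening; it cites a method without stating the denominator.

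**Conclusion.** The concern holds for the second-stage model and not for the initial unadjusted intent-to-treat test. As written, 17 of 61 candidates exist only in the valve arm. If any of them enters, the treatment term is either a non-randomised contrast or not estimable. That follows from algebra and needs no assumed figure.

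The size and direction of the bias do rest on assumptions. With lobar exclusion rates of 0.3 to 0.7 and FEV1 inputs from the article, power for the treatment term is 0.73 to 0.28 in Scenario A, and one-sided type I error is 0.14 to 0.34 in Scenario B. If patients with and without lobar exclusion do not differ, there is no bias. The figures show what the rule permits; they do not predict what this trial would find. The correction should be made because the model is attached to the superiority claim for both co-primary endpoints.

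**What to change.** 1. Limit the adjusted superiority model for each co-primary endpoint to pre-randomisation terms fixed in advance: arm, baseline value of that endpoint and the randomisation strata.
2. Move the starred variables of Tables 7 and 8, and all of Table 9, to exploratory analyses within the valve arm.
3. Reword the sentence on keeping the treatment effect to say that the arm term is always retained in this baseline-only model, and that success is decided by the pre-specified intent-to-treat comparison.
4. Test treatment interactions only for pre-randomisation covariates, label them exploratory, and state that the multiplicity correction counts every candidate screened.

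The cost is a change of wording in the Analysis section; no data are lost. Mechanism and learning-curve results remain available, but as within-arm exploratory findings that cannot support the superiority claim.

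### Continuous response predictors that show a treatment interaction are to be followed up by sub-sets; reporting the effect along the covariate from the model already fitted would be more precise and nearly free

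*Protocol article*

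**What the plan says.** The Analysis section of the protocol article sets out a sequence for finding predictors of response.

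- **Screening.** Candidates from Tables 6 to 9 are tested one at a time: "Main effects and interactions with a p-value of 0.15 or less are allowed to enter a multivariate analysis". This is the only significance level printed for covariates.
- **Mixed model, then sub-groups.** Variables with "statistically significant interactions with the treatment arm via the mixed model analysis will be further analyzed in follow-on sub-group analyses".
- **Restriction.** To contain multiple testing, "univariate sub-set analysis will be performed using only those independent variables that remain in the mixed model as interactions with the treatment arm".
- **Type I error.** "For those analyses performed on the remaining independent variables, appropriate adjustments will be made to account for impact on Type I error"; the method is given by reference.

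Table 6 consists of lung volumes, percent-predicted values, ratios, destruction scores and heterogeneity differences; the fissure score, with three levels, is the exception. Table 7 adds age, walk distance, cycle ergometry, BMI, diffusing capacity and blood gases.

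Some boundaries are printed. The footnote to Table 10 gives "Low Exercise Capacity by Cycle Ergometry ≤ 25 W for Women, ≤ 40 W for Men" for the NETT strata. Table 8 has a composite defined as "Lobar Exclusion = Yes AND Fissure Score = 3 AND RV % Predicted ≥ 200% vs. all others" and bands for operator experience, but these apply to the treatment arm only. For most continuous two-arm candidates the article gives no boundary.

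**The concern.** A sub-set analysis of a continuous variable requires grouping it. By then the mixed model has estimated how the valve effect changes with that variable. Grouping replaces the estimated slope with a step, treats patients just either side of the boundary as different, and treats all patients within a group as alike. It also divides the smaller arm: 270 patients at 2:1 gives 90 controls, or about 45 in each half of a median split.

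This matters because the Rationale section makes finding the patient characteristics that affect outcome a study aim, and the Analysis section justifies 2:1 allocation partly by better sub-group comparisons. The follow-on results are how the trial would tell clinicians which patients benefit. A less precise summary can seem to contradict a real interaction. If the boundary were picked after seeing the data, it could also seem to corroborate a false one.

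**Working it through.** The article gives no figure for this step, so there is none to reproduce.

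**Inputs.** From the Analysis section: 270 patients at 2:1, so 180 EBV and 90 control; screening level 0.15. Assumed: normal covariate and errors, equal variances, two-sided 0.05 for interaction tests, true slope differences of 0.3 and 0.4 outcome SD per covariate SD. The level at which an interaction counts as significant is not printed, so 0.05 is used, with 0.15 as the loose bound.

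**1. Information kept by a median split.** This is the squared correlation between the covariate and its high/low indicator.
- Normal: correlation = 0.3989 / 0.5 = 0.798; squared = 2/π = 0.637. Loss 36%.
- Uniform on 0 to 1: covariance = 3/8 − 1/4 = 1/8; squared correlation = (1/64) / (1/12 × 1/4) = 0.75. Loss 25%.

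**2. Power of the interaction test, continuous against median split.** The standard error of the slope difference is √(1/180 + 1/90) = 0.129 SD.
- Slope 0.4: 0.4/0.129 = 3.10, power Φ(3.10 − 1.96) = 0.87. After the split: 3.10 × 0.798 = 2.47, power Φ(0.51) = 0.70. Simulated: 0.87 and about 0.68.
- Slope 0.3: 0.3/0.129 = 2.32, power Φ(0.36) = 0.64. After the split: 2.32 × 0.798 = 1.85, power Φ(−0.11) = 0.46. Simulated: about 0.62 and 0.43 to 0.45.

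Detection takes place in the mixed model, so the first figure of each pair applies to detection. The second applies only to the follow-on split.

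**3. Agreement between the two steps.** Among simulated trials in which a real interaction passed a 0.05 gate, a median-split test at 0.05 then failed in about 25% (slope 0.4) and 36% (slope 0.3).

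**4. False findings per predictor with no true interaction.** The searched cut is the best of seven, at the 20th to 80th percentiles.

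| Route | Rate |
|---|---|
| Continuous test alone | 0.047 |
| Fixed median split alone | 0.049 |
| Searched cut, no gate | 0.19 |
| Searched cut after a 0.05 gate | 0.04 to 0.05 |
| Searched cut after a 0.15 gate | 0.10 to 0.11 |

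Over other search grids the gated rates were 0.036 to 0.046 (0.05 gate) and 0.08 to 0.13 (0.15 gate).

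**5. Value as confirmation.** Once a predictor has falsely passed a 0.05 gate, the searched cut is significant about 90% of the time (77% to 99% across grids), against about 41% for a fixed median split. The second look uses the same data as the first.

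**The case against.** Two stronger readings are tempting, and the document supports neither.

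**That the plan multiplies false findings.** A reader might take the 0.19 for an ungated search and say that the error rate almost quadruples (0.19/0.05 = 3.9). But the article allows sub-set analysis only for variables that remain as treatment interactions, and with that gate the rate is near nominal, or about double at the loosest level. The article also promises Type I error adjustment. Searching would exaggerate a finding already made; it would not create many new ones.

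**That the plan loses power to find predictors, or will pick its cuts on the data.** The article describes no dichotomising before the interaction test, so detection keeps its power. It mentions neither median splits nor data-chosen boundaries. Cut-points are commonly left to the full protocol or analysis plan, so their absence here is not a fault. The boundaries it does print are fixed in advance, and the abstract says that response predictors were defined a priori.

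It can also be said that sub-groups are easy to read, and that a fitted line is right at every covariate value only if its form is right. That is fair, and sub-group estimates can serve as a check on linearity. It does not justify making them the main follow-on result. The loss in step 1 arises even with a cut fixed in advance, and an adjustment for Type I error does not restore precision.

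**Conclusion.** The point holds as a minor one about secondary analyses. Sub-set analysis is the stated follow-up to an interaction, and it is a poor fit for the continuous variables that make up most of the two-arm candidates.

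The cost is in the follow-on description: 25% to 36% of the information on the interaction for a median split, and roughly 25% to 36% of truly detected interactions not confirmed by it, at the assumed slopes of 0.4 and 0.3. These two similar ranges measure different things. A boundary chosen on the data, if one were used, would offer no independent support.

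The figures rest on the assumed covariate distributions, slopes and test level, and on a median split as the example. They are per predictor; multiplicity across the many screened predictors is a separate matter. Detection of interactions and the rule that both primary endpoints must succeed are untouched.

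**What to change.** For continuous covariates, state that the main follow-on result is the EBV-minus-control effect with its 95% CI, taken from the same mixed model at the 10th, 25th, 50th, 75th and 90th percentiles of the covariate, with a plot. Add a check of the linear form of the interaction. Limit sub-set splits to categorical variables and to cut-points fixed before the data are seen, such as those printed in Tables 8 and 10.

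The cost is a change of wording, with no new data. The drawbacks are that readers must take the result from a curve or percentile table instead of two groups, and that the estimates depend on the fitted form of the interaction.

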**Methods:**

The trial design posted on Clinical trials.gov, on August 10, 2005 proposed an enrollment of 270 subjects. Inclusion criteria included: diagnosis of emphysema with forced expiratory volume in one second (FEV_1_) < 45% of predicted, hyperinflation (total lung capacity measured by body plethysmography > 100%; residual volume > 150% predicted), and heterogeneous emphysema defined using a quantitative chest computed tomography algorithm. Following standardized pulmonary rehabilitation, patients were randomized 2:1 to receive unilateral lobar placement of endobronchial valves plus optimal medical management or optimal medical management alone. The co-primary endpoint was the mean percent change in FEV_1 _and six minute walk distance at 180 days. Secondary end-points included mean percent change in St. George's Respiratory Questionnaire score and the mean absolute changes in the maximal work load measured by cycle ergometry, dyspnea (mMRC) score, and total oxygen use per day. Per patient response rates in clinically significant improvement/maintenance of FEV_1 _and six minute walk distance and technical success rates of valve placement were recorded. Apriori response predictors based on quantitative CT and lung physiology were defined.

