### Analysis

The power analysis is based on a pilot study in 38 patients in which FEV_1 _improved 14.9% ± 33.7 (mean ± SD) and 6 MWT distance improved 20.4% ± 41.5%. The samples size required to detect a 15% improvement in the treatment arm in FEV_1 _and a 17% improvement in 6 MWT distance at an alpha of 0.05 and a power of 0.90 is a minimum of 270 subjects with a 2:1 randomization to EBV procedure. Both of these values are above the threshold for minimal clinically important differences for these tests[17-19].

The study is designed as a superiority trial. For the two primary outcomes, the study is only considered a success if both endpoints show an improvement (one-sided test at p < 0.025). A one-sided test is appropriate to test for superiority. The actual probability of a false positive is lower than 0.025 given the imperfect correlation of the two endpoints. If change in FEV1 and change in 6 MWT were independent, the probability of a false positive would be 0.025*0.025 = 0.000625. In the pilot study generating the null hypothesis, the correlation coefficient between the change in FEV1 and 6 MWT was 0.3889. Given this r, the alpha for achieving a positive outcome is actually 0.005 (0.025*0.025^(1/(1+0.3889))). This is an assurance of avoiding a false positive well beyond convention.

The 2:1 randomization is chosen to enhance enrollment and increase the EBV population numbers in order to study covariates of treatment response. Although the 2:1 randomization increases the number of subjects required for the study, more robust subgroup comparisons may be possible.

For safety the 95% upper confidence interval for the Major Complication Composite rate delta between the EBV arm and the control arm is ≤ 30%.

The primary analysis cohort is intent to treat. As such, all 180 day missing data will be imputed using either a regression methodology if 30 and 90 day data are present or hot-deck imputation if there are not multiple datapoints available for a particular subject for regression analysis. Three unbiased imputations will be performed and the imputation resulting in the highest p-values will be selected as the final intent to treat dataset.

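### Subset analyses are adjusted only over variables that survive same-data interaction screening, which leaves the selection from 44 candidates uncorrected

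*Protocol article*

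**What the plan says.** All of this is in the protocol article, mostly in the Analysis section of Methods.

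- The candidates in Tables 6 to 9 go through univariate screening: "Main effects and interactions with a p-value of 0.15 or less are allowed to enter a multivariate analysis" (a mixed linear model).
- Variables whose interaction with treatment is statistically significant in that model go on to subgroup analysis. No significance level is given for this step.
- As a stated means of limiting multiple testing, "univariate sub-set analysis will be performed using only those independent variables that remain in the mixed model as interactions with the treatment arm".
- The next sentence reads: "For those analyses performed on the remaining independent variables, appropriate adjustments will be made to account for impact on Type I error". It cites a reference and names no method.
- The same procedure is extended to the secondary endpoints.
- The abstract says: "Apriori response predictors based on quantitative CT and lung physiology were defined".

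The Rationale for VENT names finding characteristics that affect the outcome as an additional aim. The Analysis section gives study of response covariates as one reason for 2:1 randomization.

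**The concern.** A variable reaches the subset stage because its interaction looked large in these patients. The subset tests then reuse the same data. If three variables survive out of 44, dividing the level among three treats them as if they had been the only ones examined.

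The interaction and the subset effect are also strongly related. When the treatment effects in two equal halves differ by chance, one half tends to show an apparent benefit. Selecting on the first therefore raises the chance of finding the second.

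At stake is the trial's account of who responds. A surviving subset benefit would be presented as adjusted for multiplicity, and readers would take it as error-controlled. Listing the candidates in advance does not help here: the list is prespecified, but the survivors are not.

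**Working it through.** **Plan's own figures.** The article states no error rate for predictor or subset claims, so there is none to reproduce. Its design inputs are a sample size "at an alpha of 0.05 and a power of 0.90 is a minimum of 270 subjects with a 2:1 randomization to EBV procedure" and a "one-sided test at p < 0.025". Its sample size is roughly reproducible. With control n = (1.96 + 1.2816)² × SD² × 1.5 / δ²:
- FEV1 (SD 33.7, δ 15): 79.6, rounded up to 80, total 240; power 93.2% at 270.
- 6MWT (SD 41.5, δ 17): 93.9, rounded up to 94, total 282; power 88.7% at 270.

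The check below uses 180:90 and the stated endpoint correlation of 0.3889.

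**Candidate count.** Only variables that exist in both arms can interact with arm.
- Table 6: 11 physiology entries and 17 CT entries (rows marked in two columns are calculated twice) = 28.
- Table 7, unstarred: 13.
- Table 8, unstarred: 3.
- Table 9: none; both rows are treatment-arm only.

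Total 28 + 13 + 3 = 44, and 44 × 2 endpoints = 88 interaction tests. Counting each as one test is a simplification, since Site and Target Lobe have several levels and the RUL–RML row applies to one subset only.

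**Screening with no true effects.** Expected entries at 0.15: 44 × 0.15 = 6.6 per endpoint. Assuming 0.05 two-sided retention and independent candidates:
- one endpoint: 1 − 0.95^44 = 0.895;
- two endpoints, treating all 88 tests as independent: 1 − 0.95^88 = 0.989, with 88 × 0.05 = 4.4 false interactions expected.

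**Why the subset test is not a fresh test.** For two equal halves with independent effect estimates of variance v, the correlation between one half's effect and the interaction is v / √(v × 2v) = 0.707. Suppose a variable is just retained, with interaction z = 2.0. The favoured half's z then has mean 0.707 × 2.0 = 1.41 and SD √0.5 = 0.707. Even if it is the only survivor and both its subsets are corrected for (one-sided 0.0125, critical z 2.24), P(false claim) = P(Z > (2.24 − 1.41)/0.707) ≈ 0.12, not 0.025.

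**Simulation of the whole path**, with no true effects: entry at 0.15, retention at 0.05, one-sided tests in the two subsets of each survivor.

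| At least one false interaction | Rate |
|---|---|
| One endpoint, all scenarios | 0.51–0.92 |
| Two endpoints, independent candidates | 0.97–0.99 |
| Two endpoints, correlated candidates | 0.75–0.98 |
| Two endpoints, only 20–30 candidates | 0.81–0.96 |

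| At least one false subset efficacy claim | Rate | Rate / 0.025 |
|---|---|---|
| Bonferroni over all survivor subset tests, binary covariates | 0.167–0.181 | 6.7–7.3 |
| Same, continuous covariates split at the median | 0.10–0.13 | about 4–5 |
| One endpoint only, continuous covariates | 0.07–0.12 | about 3–5 |
| Correction per variable or within each endpoint | 0.17–0.40 | about 7–16 |
| No adjustment of survivors | 0.24–0.58 | about 10–23 |

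The last row matters because "For those analyses performed on the remaining independent variables, appropriate adjustments will be made to account for impact on Type I error" could be read as covering the variables that were not retained. The survivors would then have no stated correction.

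**After correction over the full set.** Bonferroni over 44 × 2 subsets × 2 endpoints = 176 subset tests gives false subset claims in about 0.004–0.015 of trials (continuous-covariate scenarios).

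**The case against.** The strongest reply has four parts.

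1. *The adjustment is left to another document.* The article names no method, and the full protocol or analysis plan may supply one. That is fair for the method, the retention level and the cut-points, and their absence is not criticized here. But the article does fix which analyses are adjusted and offers the restriction to survivors as the safeguard. That rule gives the wrong result whichever standard method is applied over survivors.

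2. *The restriction does help.* This stands. A reader might infer that the stated protection is empty, but the text claims only to limit multiplicity. In a one-endpoint check, testing every candidate subset unadjusted gave a false claim in 37–40% of trials, against 9–18% with the gate and an adjustment over survivors.

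3. *The candidates overlap heavily.* This also stands. RV is derived from TLC and FVC or VC, ratios and BODE reuse listed variables, several rows restate the target lobe, and CT scores appear twice. A reader might call a false predictor near certain. That holds only for nearly independent candidates or both endpoints pooled. With one endpoint and blocks of six candidates correlated at 0.9, the rate was 56%.

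4. *The inflation depends on how one divides.* A reader might settle on seven to eight times nominal as a fixed figure. Part of such a figure can come from dividing 0.025 by the number of surviving variables when each gives two subset tests. In one setting with median splits, dividing by variables gave about 17.5%, while dividing by the actual tests gave 9.2–11.9%. Only a range is defensible.

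**Conclusion.** The point holds as a flaw in a stated rule. Adjusting only over data-selected survivors does not control the error rate for predictor or subset claims, and every scenario examined exceeded the nominal 2.5% several-fold.

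The size rests on assumptions the article does not supply: retention at p < 0.05, binary or median-split subsets, Bonferroni over survivors, and no true effects. Under these, a false interaction is likely to near certain (about 50–90% of trials for one endpoint, 75–99% for two, depending on correlation among candidates). A false subset efficacy claim occurs in roughly 7–18% (about 3 to 7 times nominal), and in more if the correction is made per variable or within each endpoint.

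A reader might infer that the trial's efficacy conclusion is compromised. The article does not support that: success requires both co-primary tests to pass, and no subset claim enters that decision. It is worth correcting because responder identification is a declared aim.

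**What to change.** Replace the adjustment sentence with wording to this effect:

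*Treatment-by-covariate interaction p-values are adjusted over all two-arm candidates in Tables 6 to 8 and both co-primary endpoints, by Holm's method or by a permutation maximum statistic that repeats the whole screening. A subset result is reported as a finding only if its interaction is significant after this adjustment. All other subset results are labelled exploratory.*

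Both endpoints must be in the family. Correcting over 44 at 0.05 for each endpoint separately allows up to about 10% across the two. Over 88 tests the bound is 88 × (0.05/88) = 5%, and since a subset finding requires a passing interaction, false subset findings cannot exceed that bound when there are no true effects. If 2.5% is wanted for them too, set the family level at 0.025. The permutation version loses less to the overlap among candidates.

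The change needs analysis wording and some computing; the cost is power. For an illustrative half-split on FEV1 (90:45 in each half), the SE of a subset effect is 33.7 × √(1/90 + 1/45) = 6.15, and the SE of the interaction is 6.15 × √2 = 8.70. At 80% power (chosen here for illustration), the detectable interaction rises from (1.96 + 0.84) × 8.70 = 24.4 percentage points unadjusted to (3.45 + 0.84) × 8.70 = 37.3 at 0.05/88. Both exceed the 15% effect the trial is sized for, so reliable detection of modest interactions was not available in any case. Subsets labelled exploratory keep their hypothesis-generating value.
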